#### **Grade**

All adverse events will be graded according to the NCI Common Terminology Criteria for Adverse Events (CTCAE) version 4.03. The CTCAE v4.03 is available at <http://ctep.cancer.gov/reporting/ctc.html>

If no CTCAE grading is available, the severity of an AE is graded as follows:

Mild (grade 1): the event causes discomfort without disruption of normal daily activities.

Moderate (grade 2): the event causes discomfort that affects normal daily activities.

Severe (grade 3): the event makes the patient unable to perform normal daily activities or significantly affects his/her clinical status.

Life-threatening (grade 4): the patient was at risk of death at the time of the event.

Fatal (grade 5): the event caused death.

#### **Relationship**

Attribution categories for adverse events in relationship to treatment are as follows:

Definite – The AE *is clearly related* to the study treatment.

Probable – The AE *is likely related* to the study treatment.

Possible – The AE *may be related* to the study treatment.

Unlikely – The AE *is doubtfully related* to the study treatment.  
Unrelated – The AE *is clearly NOT related* to the study treatment.

### **Seriousness**

A serious adverse event is an undesirable sign, symptom or medical condition which:

- 
- is fatal or life-threatening
  - required or prolonged hospitalization
  - results in persistent or significant disability/incapacity
  - constitutes a congenital anomaly or a birth defect
  - is medically significant, may jeopardize the subject and may require medical or surgical intervention to prevent one of the outcomes listed above.
- 

Events not considered to be serious adverse events are hospitalizations for the:

- routine treatment or monitoring of the studied indication not associated with any deterioration in condition.
  - elective or pre-planned treatment for a pre-existing condition that did not worsen.
  - treatment on an emergency, outpatient basis for an event not fulfilling any of the definitions of serious given above and not resulting in hospital admission.
- 

### **5.4.3 Prior experience**

Expected events are those that have been previously identified as resulting from administration of the agent. An adverse event is considered unexpected, for expedited reporting purposes only, when either the type of event or the severity of the event is not currently known.

### **5.4.4 Expedited Reporting**

The Principal Investigator must be notified within 24 hours of learning of any serious adverse events, occurring during the study.

The UCSD Human Research Protections Program (HRPP) must be notified within 10 business days of “any unanticipated problems involving risk to subjects or others” (UPR).

Avera McKennan Cancer Institute Regulatory Department will be notified within 10 business days of “any unanticipated problems involving risk to subjects or others” and inform UCSD within the same time interval.

#### **5.4.5. The following events meet the definition of UPR:**

- Any serious event (injuries, side effects, deaths or other problems), which in the opinion of the Principal Investigator was unanticipated, involved risk to subjects or others, and was possibly related to the research procedures.
- Any serious accidental or unintentional change to the IRB-approved protocol that alters the level of risk.

- Any deviation from the protocol taken without prior IRB review to eliminate apparent immediate hazard to a research subject.
- Any new information (e.g., publication, safety monitoring report, updated sponsor safety report), interim result or other finding that indicates an unexpected change to the risk/benefit ratio for the research.
- Any breach in confidentiality that may involve risk to the subject or others.
- Any complaint of a subject that indicates an unanticipated risk or that cannot be resolved by the Principal Investigator.

#### **5.4.6 Instructions for routine reporting of adverse events:**

The UCSD HRPP will be notified of any adverse events that are not unanticipated problems involving risk to subjects or other (non-UPRs) at the time of the annual Continuing Review.

## **6 STATISTICAL CONSIDERATIONS**

---

### **6.1 Study Design**

This is a prospective, open label navigational investigation to evaluate the feasibility of using molecular profile-based evidence to determine individualized cancer therapy for patients with incurable malignancies. This is a non-randomized, histology-agnostic trial. Although there will be a case mix of histologies, we now know that individual histologies are composed of a heterogeneous mix of genomic alterations. It is not clear that one case mix is better or worse than another. Thus, we are testing a strategy of molecular matching that may apply across cancers. All eligible and consented patients will have their tumor tissues/blood genomic profiled by Foundation Medicine's FoundationOne™ genomic analysis. Patients will be stratified into Group 1 (treatment naïve, unresectable/medically unfit for surgery), Group 2 (treatment naïve, metastatic), and Group 3 (prior treated), respectively. Following analysis for genomic alterations, matched therapy, if available, will be recommended by the Study Committee or Molecular Tumor Board. If the patients received the matched therapy, they are designated as in Arm A. Otherwise, if the patients received the unmatched therapy (i.e., treating physician's choice of traditional systemic chemotherapy), they are designated as in Arm B. The study feasibility will be measured by the ability to enroll patients, the acceptable turnaround time and the actionable information obtained from the genomic profiling, and the viability of identifying and delivering the matched therapy. The treatment efficacy will be determined among the patients groups and treatment arms. The safety profile of the treatment will be assessed as well.

## **6.2 Sample Size and Accrual**

This is a feasibility study with descriptive analysis as the primary analysis to characterize the study findings. We plan to enroll a total of 150 patients in Groups 1 and 2 and an unlimited number of patients in Group 3 (of up to 1000 patients) with their blood/tissues subject to the FoundationOne™ assay. We project to enroll patients in 30 months plus additional 6 months of follow-up. The total study period is 3 years. We expect that the accrual rate is 2 patients per month for Groups 1 and 2, and 4 patients per month for Group 3 in the first year. After the study mechanism is established and if we begin to see objective responses with matched therapy, we expect these rates to increase to 3 patients per months for Groups 1 and 2, and 5 patients per month for Group 3 in subsequent years. The total and percent of patients in Arm A and Arm B for each group will be determined to assess the feasibility of this study. With the comprehensive genomic profiling, we expect that 40% of the patients (N=30) will be in Arm A and 60% of the patients (N=45) will be in Arm B for all three patients groups.

## **6.3 Statistical Methods**

This is a hypothesis-generating trial and not a hypothesis-driven trial. We will collect data prospectively by running concurrent trials (e.g., Groups and Arms) and describing outcomes. We will then analyze the data.

Therefore, the primary statistical analysis is descriptive in nature. Due to the moderate size of the study, the statistical analysis is primarily exploratory and descriptive rather than definitive. The information gathered in this exploratory study will be used for designing future confirmative studies. Summary statistics such as the frequency counts for the categorical variables and minimum, maximum, median, mean, and standard deviation for continuous variables will be computed. In addition, for the analyses of exploratory endpoints, Kaplan-Meier analyses will be computed to estimate the survival rate for time-to-event endpoints. Estimation with both point estimator and 95% confidence estimation for the study endpoints will be provided. Hypothesis testing with appropriate statistical methods will be performed as indicated. For example, Fisher's exact test and chi-square test will be applied to test equal proportion among groups for categorical data such as the response status. Two-sample t-test and Wilcoxon rank sum test will be used to assess the distribution of continuous variable such as the tumor regression percentage between two independent groups. Analysis of variance (ANOVA) and Friedman's test will be applied to assess the distribution of continuous variable among 3 or more groups. Log-rank test and Cox regression model will be applied for comparing the time-to-event endpoints between groups.

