Patients for whom we are unable to procure a matched treatment will be considered ARM B in each group. ARM B patients will receive treating physician's choice of traditional systemic chemotherapy treatment for their malignancy, defined by National Comprehensive Cancer Network (NCCN) guidelines and/or tumor board recommendation(s). If there is no standard of care treatment, the treating physician may select a regimen based upon published reports, series, and/or clinical trials.

Patients with no actionable alterations by FoundationOneTM will receive treating physician's choice of traditional systemic chemotherapy treatment for their malignancy, defined by National Comprehensive Cancer Network (NCCN) guidelines and/or tumor board recommendation(s). If there is no standard of care treatment, the treating physician may select a regimen based upon published reports, series, and/or clinical trials.

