## **6.4 Sample Size Calculation**

All exploratory analysis will test the hypothesis of greater response rate in Arm A than that in Arm B. With an estimated sample size of 30 (ARM A) and 45 (ARM B) in each group, we can estimate the response rate with a standard error no larger than 0.09 and 0.07, respectively. We will have sufficient statistical power to detect the difference between groups only if the difference between groups is sufficiently large. For example, with the sample size of 30 and 45 for Arm A and Arm B, we will have 79% power to detect the response rate of 0.25 and 0.05 between the two arms with one-sided 10% type I error rate using the continuity corrected chi-square test.

We will have more than 80% power to detect the difference between Arm A and Arm B using the log-rank test when the median PFS is 4 months and 2 months for the two arms, respectively.

In addition, in Group 1A, we will estimate the proportion of patients who are initially unresectable (as deemed by two surgeons) but converted to resectable (as deemed by two surgeons) after 8 weeks of the matched treatment, or if ever resected. With 30 patients, we expect to see at least one patient becomes resectable with a probability of 0.79, 0.96, and 0.99 if the conversion rate is 0.05, 0.10, and 0.15, respectively. We expect to see at least 2 patients become resectable with a probability of 0.82 and 0.95 if the conversion rate is 0.10 and 0.15, respectively. One-sided nominal level at 10% will be used to declare statistical significance. No P value adjustment for multiplicity will be applied due to the exploratory nature of the study. All study results need to be confirmed by future studies with larger sample sizes.

- The response rate (proportion of patients reaches CR or PR) will be estimated based on RECIST for each patient group and each treatment arm.
- The tumor regression rate (in %) will be calculated by the percent tumor size reduction from baseline to after treatment will be determined in and across patient groups.
- Progression-free survival (PFS) and overall survival (OS) will be determined in and across patient groups and treatment arms.

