- The results of PFS and OS outcomes will be described relative to historical controls or published data. Due to the potential difference in patient populations between the current study and historical controls, we will also perform multivariate analyses to adjust the difference in prognostic factor(s) when comparing the PFS and OS between the different cohorts.
- The treatment grade 3-5 adverse events will be documented and analyzed by descriptive statistics.

As described earlier, this is a feasibility and descriptive study that will generate preliminary data for designing future studies. The exact numbers of patients in Arm A and Arm B for each group correspond to the feasibility endpoints. Although these numbers are unknown in the design stage, with the comprehensive genomic profiling and dedicated efforts in finding and securing the matched therapy, we expect that 40% of the patients (N=30) will be in Arm A and 60% of the patients (N=45) will be in Arm B for all three patients groups.

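### Response in Arm A versus Arm B is tested only without adjustment although the arms are formed by treatment received; case mix can distort the result, modestly in Groups 1 and 2 and materially if Group 3 becomes large.

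*Protocol*

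**What the plan says.** The protocol gives response a directional hypothesis (section 6.4, repeated in 6.6): "All exploratory analysis will test the hypothesis of greater response rate in Arm A than that in Arm B". It adds a decision rule: "One-sided nominal level at 10% will be used to declare statistical significance", without multiplicity adjustment. The only tests named for response, in sections 6.3 and 6.5, are Fisher's "exact test and chi-square test will be applied to test equal proportion among groups for categorical data such as the response status". The power statement rests on the same kind of unadjusted test: "we will have 79% power to detect the response rate of 0.25 and 0.05 between the two arms", "using the continuity corrected chi-square test".

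Arms follow treatment received (section 6.1). The section on the Molecular Tumor Board states: "Patients for whom we are unable to procure a matched treatment will be considered ARM B in each group". Under Treatment Decisions the treating physician has the final choice, and under Insurance Coverage a denial leads to physician's choice of chemotherapy.

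Multivariate adjustment is stated once, in identical words in sections 6.4 and 6.6, for PFS and OS: "when comparing the PFS and OS between the different cohorts". Nothing comparable is stated for response.

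On size, the protocol expects 30 and 45 patients in Arms A and B of every group, yet section 6.2 allows "an unlimited number of patients in Group 3 (of up to 1000 patients".

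**The concern.** Access to a matched drug depends on the alteration found, the drugs approved or on trial, the insurer and the physician. Several of these plausibly vary with tumour type, and tumour types differ in prognosis: Figure 1 gives stage IV two-year mortality from 52.1% (breast) to 94.8% (gallbladder). Analysing by Group separates untreated from pretreated patients, but not tumour types, ECOG 0 from 1, or one prior line from several.

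If the arms differ in a factor related to response, the unadjusted test measures that difference along with any effect of matching. Unlike chance error, this bias does not shrink as patients are added, so the rejection rate drifts further from nominal. Section 6.3 says that the results will be used to design confirmatory studies. A confounded difference could therefore become the next trial's effect assumption.

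**Working it through.** **Step 1. Reproduce the plan's figure.** Inputs from section 6.4: n = 30 and 45, response 0.25 and 0.05, one-sided α = 0.10 (z = 1.2816), continuity correction.

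- Pooled rate: (30×0.25 + 45×0.05)/75 = 0.13
- SE under the null: √[0.13×0.87×(1/30 + 1/45)] = 0.0793
- SE under the alternative: √[0.25×0.75/30 + 0.05×0.95/45] = 0.0855
- Correction: ½(1/30 + 1/45) = 0.0278
- z = (0.20 − 0.0278 − 1.2816×0.0793)/0.0855 = 0.826, power 79.6%

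The stated 79% is reproduced. The power figure is not at fault.

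**Step 2. Arm sizes.**

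- 30/45: stated for all three groups.
- 55/83: Group 3 at the stated accrual, 12×4 + 18×5 = 138 patients, split 40/60.
- 400/600: Group 3 at the cap of 1000, split 40/60.
- 200/300: 1000 profiled patients with 50% actionable (lower end of the expected 50-70%), 40% of those matched, and non-actionable patients placed in neither arm.

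**Step 3. Assumed case mix (not in the documents).** No treatment effect in either tumour class. Response 5% in GI and 20% in non-GI tumours; GI share 50% in A and 70% in B. At 400/600 the overall GI share is (200 + 420)/1000 = 62%, within the eligibility cap of 65%.

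- Expected response in A: 0.5×0.05 + 0.5×0.20 = 0.125
- Expected response in B: 0.7×0.05 + 0.3×0.20 = 0.095

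With a milder contrast (10% and 20%) the rates are 0.15 and 0.13.

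**Step 4. Rejection rates.** Worked case, 400/600: pooled rate 0.107; SE under the null 0.01995; SE under the alternative 0.02041; correction 0.00208; z = (0.030 − 0.00208 − 1.2816×0.01995)/0.02041 = 0.115, which gives 54.6%. Exact binomial enumeration gives 54.4%. Exact results for the continuity-corrected chi-square at one-sided 10%:

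| Scenario | 30/45 | 55/83 | 200/300 | 400/600 |
|---|---|---|---|---|
| No imbalance (62% GI in both) | 5.9% | 6.4% | 7.7% | 8.3% |
| 5% v 20%, GI 50% v 70% | 12.6% | 16.8% | 35.7% | 54.4% |
| 10% v 20%, GI 50% v 70% | 9.6% | 11.9% | 22.1% | 31.7% |
| 5% v 20%, GI 55% v 65% | 8.8% | 10.7% | 18.6% | 26.3% |
| 5% v 20%, reversed (70% v 50%) | 2.4% | 1.9% | 0.6% | 0.2% |

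**Step 5. Stratified alternative.** In the 5% v 20%, 50% v 70% scenario (200,000 simulated trials per size), a Mantel-Haenszel test stratified by GI/non-GI rejects in 10.0-10.5% of trials across the four sizes. With a continuity correction it rejects in about 5-8%.

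**Step 6. Can the data carry adjustment?** Expected responders at the plan's 0.25 and 0.05:

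- 30/45: 7.5 + 2.25 = 9.75
- 55/83: 13.75 + 4.15 = 17.9
- 200/300: 50 + 15 = 65
- 400/600: 100 + 30 = 130

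One stratifier is workable throughout. A model with several covariates is realistic only in a large Group 3.

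**The case against.** The strongest reply is scope. Response is an exploratory endpoint, the analysis is called descriptive and hypothesis-generating, arm efficacy is to be described, and all results need confirmation. The tests are introduced as examples, and covariates are often left to a SAP, which is not at hand. This stands as a reason for lower severity. It does not remove the point, because the protocol itself fixes a directional hypothesis, a significance level and an unadjusted test for it.

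Three stronger readings are tempting and not supported:

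- A reader might infer that the planned test rejects in 22%, 25% and 59% of trials at 30/45, 55/83 and 400/600. Those are the rates of an uncorrected z-test, which already rejects in 12% at 30/45 with no imbalance. The test behind the power statement is continuity-corrected and gives 12.6%, 16.8% and 54.4%.
- A reader might infer that the protocol deliberately adjusts the arm comparison for survival but not for response. The PFS/OS sentence is prompted by differences from historical controls, and it is unclear whether the cohorts it mentions include Arm A versus Arm B.
- A reader might take 400/600 as the planned size. It is one reading of the cap. The stated accrual gives 138 patients in Group 3, and 50-70% actionable with 40% of those matched would put 200-280 of 1000 patients in Arm A.

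It is also fair that the imbalance and its direction are assumed, and that a GI-stratified test holds its level here because GI status is the only confounder simulated.

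**Conclusion.** The point holds in limited form. The only tests the protocol names for its directional response hypothesis ignore case mix, between arms formed by treatment received. Under the assumed imbalance in Arm A's favour, rejection at 30/45 is 10-13% against about 6% without imbalance, a modest distortion that is close to or slightly above the nominal 10%. It becomes material only if Group 3 grows: 22-36% at 200/300 and 32-54% at 400/600, against about 8%. If the imbalance runs the other way, the test is too conservative and can hide a real effect. The documents do not show which direction applies, nor that an imbalance of this size will occur. Given the exploratory endpoint, this is a change to consider.

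**What to change.** Make the Arm A versus Arm B response comparison a Mantel-Haenszel test stratified by tumour type (GI/non-GI), and state whether a continuity correction is used. Use only this stratifier in Groups 1 and 2. In Group 3, if responder numbers allow, add a logistic model (Firth's penalised likelihood if sparse) with tumour type, ECOG 0/1 and number of prior lines. Keep the crude response rates by group and arm as description. State that selection by drug access, insurance and physician choice is not removed by these adjustments, so that a small adjusted p-value is not over-read. Reconcile the Group 3 cap with the stated accrual and the 30/45 arm sizes, since these decide how much adjustment is possible.

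The cost is a little more analysis work and a slight loss of precision in the small groups. Diagnosis, ECOG status and oncology history are already recorded at baseline, so no extra patients or assessments are needed.

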## **Navigation to Treatment**

### **Study Groups**

Patients will be grouped into one of three study Groups (Groups 1, 2, or 3) based on their disease status and history of prior cancer therapy:

Group 1: Treatment naïve patients with unresectable disease or medically unfit for surgical resection.

Group 2: Treatment naïve patients with metastatic disease.

Group 3: Patients with metastatic or unresectable disease who have received at least one prior unmatched systemic therapy and no prior matched therapy.

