## **6.5 Planned Analyses**

This primary statistical analysis is descriptive in nature. Summary statistics such as the frequency counts for the categorical variables and minimum, maximum, median, mean, and standard deviation for continuous variables will be computed. The Kaplan-Meier curve will be computed to estimate the survival rate for time-to-event endpoints. Estimation with both point estimator and 95% confidence estimation for the study endpoints will be provided. Hypothesis testing with appropriate statistical methods will be performed as indicated. For example, Fisher's exact test and chi-square test will be applied to test equal proportion among groups for categorical data such as the response status. Two-sample t-test and Wilcoxon rank sum test will be used to describe the distribution of continuous variable such as the tumor regression percentage between two independent groups. Analysis of variance (ANOVA) and Friedman's test will be applied to describe the distribution of continuous variable among 3 or more groups. Log-rank test and Cox regression model will be applied for comparing the time-to-event endpoints between groups. However, due to the moderate size of the study, the statistical analysis is primarily exploratory rather than definitive. The information gathered in this exploratory study will be used for designing future confirmative studies.

The primary and secondary are for feasibility and will be estimated based upon four parameters:

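### Friedman's test is named for comparing three or more groups, but Groups 1 to 3 are separate, unmatched patients; the rank test that fits is Kruskal-Wallis (minor correction)

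*Protocol*

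**What the plan says.** For two groups, Protocol Section 6.3 pairs a parametric test with a rank test: "Two-sample t-test and Wilcoxon rank sum test will be used to assess the distribution of continuous variable such as the tumor regression percentage between two", and it describes those two groups as independent. The next sentence moves to three or more groups: "Analysis of variance (ANOVA) and Friedman's test will be applied to assess the distribution of continuous variable among 3 or more groups". Section 6.5 repeats it with one verb changed: "Analysis of variance (ANOVA) and Friedman's test will be applied to describe the distribution of continuous variable among 3 or more groups". Kruskal-Wallis is not mentioned anywhere in the protocol.

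The groups are mutually exclusive. Section 3.2, where they are defined, says: "Patients will be grouped into one of three study Groups (Groups 1, 2, or 3) based on their disease status and history of prior cancer" (that is, earlier treatment). Section 6.1 gives the same division: "Patients will be stratified into Group 1 (treatment naïve, unresectable/medically unfit for surgery), Group 2 (treatment naïve, metastatic), and Group 3 (prior treated), respectively". On size, Section 6.2 states: "We plan to enroll a total of 150 patients in Groups 1 and 2 and an unlimited number of patients in Group 3 (of up"; the cap it gives for Group 3 is 1000.

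The continuous outcome in view is tumor regression. Section 6.4 says: "The tumor regression rate (in %) will be calculated by the percent tumor size reduction from baseline to after treatment will be determined in and across", the sentence going on to refer to the patient groups. The Statistical Methodology entry of the Study Summary and the hypotheses in the Rationale both ask whether regression is higher in treatment-naïve patients than in previously treated ones. The significance rule in Section 6.4 is: "One-sided nominal level at 10% will be used to declare statistical significance".

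**The concern.** Friedman's test is the rank analogue of a two-way layout with one observation per cell. It ranks the conditions inside each block and discards differences between blocks. It needs every block to contribute one value to every condition. A patient in Group 1 contributes nothing to Groups 2 or 3, so no blocks exist.

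The wording around the sentence shows what was meant. The t-test and the Wilcoxon rank sum test are the parametric and rank choices for two independent groups. ANOVA and its rank counterpart should follow for three or more, and that counterpart is Kruskal-Wallis.

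At stake is whether a rank comparison of regression across the three groups can be carried out as written. An analyst who follows the text either finds that the test will not run or has to invent a pairing of unrelated patients.

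**Working it through.** No stated figure depends on this test, so there is nothing in the plan to reproduce. The check sets the test's data requirements against the design and then sizes the effect by simulation.

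**Step 1. Are there blocks?** Friedman's test with k conditions and b blocks needs a complete b × k table. Each patient falls in one group only (Study Groups; Section 6.1), and the protocol defines no matching across groups.

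**Step 2. Could the sentence refer to repeated measures?** Scans are taken about every 8 weeks, but the regression endpoint is the best percent reduction, one value per patient. The named within-patient comparison is PFS2/PFS1 in Group 3, with two values per patient. No planned analysis compares three or more values per patient.

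**Step 3. Will the groups be equal in size?** The protocol gives 150 for Groups 1 and 2 together and up to 1000 for Group 3. The accrual rates in Section 6.2 give Group 3 4 × 12 + 5 × 18 = 138 over 30 months. Section 6.2 also expects 30 + 45 = 75 in each group. Equal groups are therefore possible only if that last expectation is met exactly.
- Assumed sizes 75/75/1000 (an even split of the 150): Friedman's test returns an error because the lengths differ; Kruskal-Wallis runs.
- Assumed sizes 75/75/138: Friedman's test again returns an error.

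**Step 4. If sizes were equal, does the arbitrary pairing matter?** One simulated data set was used, with 75 per group, normal data and two groups shifted by 0.3 SD (assumed). Over 2000 random line-ups of the same data, Friedman's p ran from 0.00002 to 0.38, with a central 95% range of 0.0006 to 0.12. Kruskal-Wallis gave one value, 0.0036.

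**Step 5. Size and power with equal groups.** Both are omnibus tests without direction, so the protocol's 10% is used here simply as p < 0.10. Data are normal; the shifts are assumptions, not protocol figures.

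| Scenario | n per group | Friedman | Kruskal-Wallis |
|---|---|---|---|
| One group shifted 0.5 SD | 30 | 48–51% | 58–61% |
| One group shifted 0.5 SD | 75 | 84–85% | 93% |
| Two groups shifted 0.4 SD | 30 | 35% | 45% |
| Two groups shifted 0.4 SD | 75 | 67% | 80% |
| No shift | 30 | 9.3% | 9.4% |
| No shift | 75 | 9.5% | 10.9% |

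Ranges are over repeated simulation runs. The loss is about 8 to 13 percentage points of power. The false-positive rate is not inflated.

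**Step 6. What the other named tests do.** In the 0.5 SD scenario ANOVA has 63% power at 30 per group and 94% at 75. A one-sided Wilcoxon rank sum test of Groups 1 and 2 pooled against Group 3 has 82% and 99% if Group 3 is the shifted group. The Wilcoxon figures answer a directional two-group question and are not like for like with the omnibus tests.

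**The case against.** The best defence is that little hangs on the word. Both sections promise appropriate methods and offer the named tests only as examples. ANOVA stands in the same sentence and handles independent groups of unequal size. The one directional regression question compares treatment-naïve with previously treated patients. That is a two-group comparison, for which Section 6.3 already names the Wilcoxon rank sum test. On unequal groups Friedman's test stops with an error, so it would not quietly yield a wrong answer. All of this stands, and it limits the consequence. It does not make Friedman's test fit the design.

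A reader might infer more than the document supports:
- That the three-group comparison has no valid test. It has ANOVA.
- That the error would produce false positives. With equal groups the rejection rate under no difference stays near 10%.
- That a three-group comparison of tumor-marker change is also affected by name. Marker change is listed as an exploratory endpoint to be estimated, and Section 6.6 speaks only in general terms of comparing across groups. A three-group marker comparison is implied at most.
- That the matter belongs to a statistical analysis plan not shown here. The protocol itself names the wrong test, twice, so the correction belongs in the protocol.

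**Conclusion.** The point holds as a minor correction. Friedman's test does not fit any planned comparison in this protocol: the three groups are disjoint and unblocked, and no outcome with three or more values per patient is compared. With unequal groups it cannot be computed. With equal groups it keeps its type I error, but its p-value depends on an arbitrary ordering, and it gives up roughly 10 points of power against Kruskal-Wallis: about 50% against 60% at 30 per group, and 84% against 93% at 75 per group. Those power figures assume normal data, one group shifted by 0.5 SD and a 10% level.

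The conclusion about fit needs none of those assumptions; it follows from the group definitions. The affected analyses are exploratory and hypothesis-generating. The primary feasibility proportion and every stated sample size and power figure are untouched.

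**What to change.** In Sections 6.3 and 6.5, replace Friedman's test with the Kruskal-Wallis test and leave ANOVA as it stands. Add one sentence saying that the question of higher tumor regression in treatment-naïve patients will be addressed by the Wilcoxon rank sum test already named in Section 6.3, applied to Groups 1 and 2 together against Group 3.

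The cost is a wording change in two sentences and one added sentence. Design, sample size and data collection do not change.
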